## Abstract

**Background:**

The epidemiology of ICU pneumonia caused by *Staphylococcus aureus* (*S. aureus)* and *Pseudomonas aeruginosa (P. aeruginosa)* is not fully described, but is urgently needed to support the development of effective interventions. The objective of this study is to estimate the incidence of *S. aureus* and *P. aeruginosa* ICU pneumonia and to assess its association with patient-related and contextual risk factors.

**Methods:**

ASPIRE-ICU is a prospective, observational, multi-center cohort study nested within routine surveillance among ICU patients in Europe describing the occurrence of *S. aureus* and *P. aeruginosa* ICU pneumonia. Two thousand (2000) study cohort subjects will be enrolled (50% *S. aureus* colonized) in which specimens and data will be collected. Study cohort subjects will be enrolled from a larger surveillance population, in which basic surveillance data is captured. The primary outcomes are the incidence of *S. aureus* ICU acquired pneumonia and the incidence of *P. aeruginosa* ICU acquired pneumonia through ICU stay.

The analysis will include advanced survival techniques (competing risks and multistate models) for each event separately as well as for the sub-distribution of ICU pneumonia to determine independent association of outcomes with risk factors.. A risk prediction model will be developed to quantify the risk for acquiring *S. aureus* or *P. aeruginosa* ICU pneumonia during ICU stay by using a composite score of independent risk factors.

**Discussion:**

The diagnosis of pathogen-specific ICU pneumonia is difficult, however, the criteria used in this study are objective and comparable to those in the literature.

**Trial registration:**

This study is registered on clinicaltrials.gov under identifier NCT02413242.

**Electronic supplementary material:**

The online version of this article (10.1186/s12879-017-2739-4) contains supplementary material, which is available to authorized users.

## Background

Patients hospitalized in the Intensive Care Unit (ICU) are at risk of acquiring pneumonia, especially if they are mechanically ventilated. Despite extensive efforts, ICU-acquired pneumonia continues to be one of the most frequently occurring complications in the ICU and increases morbidity as well as mortality [1, 2]. Accurately describing and predicting the occurrence of ICU pneumonia is difficult as a result of inconsistencies in the case definition and surveillance methods in different countries [1, 3]. The need for an accurate and standardized prognosis is important considering current interventions are preventive rather than therapeutic [4]. As part of the COMBACTE consortium (COMBatting AntibiotiC resisTance in Europe), two monoclonal antibodies (mAbs) are currently being developed that target *S. aureus* and *P. aeruginosa*, respectively [5, 6]. Both bacteria are frequently occurring causative pathogens of ICU pneumonia and administration of a mAb may prevent the development of ICU pneumonia with these pathogens [7, 8]. Prospective studies can assess possible risk factors that can identify subsets of patients that may benefit most from these interventions. Thus, the goal of this study is to systematically assess the impact of patient-related and contextual factors on the incidence of *S. aureus* and *P. aeruginosa* ICU pneumonia in Europe and to identify the patient subgroups that are at greater risk for disease and bear a disproportionate disease burden. These objectives will directly contribute to the sample size and feasibility calculations for clinical trial design of the mAb interventions [8].

## Methods

### Objectives

The primary objectives of this study are to determine the incidence of:
*S. aureus* ICU pneumonia through ICU stay; and
*P. aeruginosa* ICU pneumonia through ICU stay; andtheir independent associations with patient-related factors (e.g. colonization status, baseline serum antibody levels against *S. aureus* or *P. aeruginosa* antigens) and contextual factors.

The key secondary objectives are to develop risk prediction models to quantify the risk of acquiring (i) *S. aureus* or (ii) *P. aeruginosa* ICU pneumonia during ICU stay, by using a composite score of independent risk factors identified through primary objective 1 and 2. Other secondary and exploratory objectives can be found on ClinicalTrials.gov, under identifier NCT02413242, or in the online (Additional file 1: S.01).

### Study design

**ASPIRE-ICU** (**A**dvanced understanding of ***S***
*taphylococcus aureus* and **P**seudomonas aeruginosa **I**nfections in Eu**R**op**E** - **I**ntensive **C**are **U**nits) is a multi-center, prospective, observational cohort study nested within ongoing routine surveillance among ICU patients in Europe. The study is composed of two study populations, the surveillance population and study cohort population. The study cohort is nested within the larger surveillance population; this means that all data and specimens collected specifically for study cohort participants is *in addition* to data already captured by ways of surveillance. An overview of the schedule of procedures, including all sample collection types and time points can be found in the online (Additional file 1: Table S.02).

### Study populations and recruitment

#### Surveillance population

Patients eligible to participate in the surveillance population must be on mechanical ventilation (MV) upon or (expected to be) within 24 h after ICU admission and have an expected length of stay (LOS) of at least 48 h. Patients with an expected ICU stay of less than 48 h are at a lower risk for developing ICU infections since this population is generally healthier, without significant comorbidities and shorter in the ICU.

The surveillance population are considered to be the source population from which the study cohort subjects are derived. No informed consent is required for participation in the surveillance population, but depending on local legislation, patients of the surveillance population will receive information (i.e. leaflet/flyer) on the ASPIRE-ICU study and are able to deny use of their de-identified data for scientific purposes.

#### Study cohort population

Surveillance patients that meet the eligibility criteria described below for the study cohort population will be enrolled. 2000 study cohort subjects are required to meet the objectives of this study. Study cohort subjects are approached for informed consent based on their *S. aureus* colonization status at ICU admission. Subjects will be enrolled in a 1:1 ratio of *S. aureus* colonized subjects to non *S. aureus* colonized subjects with 1000 subjects in each stratum. A similar temporal distribution of enrolled *S. aureus* colonized and non *S. aureus* -colonized subjects will be managed by selecting the first non-colonized subject after including a colonized subject. For subjects unable to provide consent for any reason, a legally accepted representative may consent on the subject’s behalf at the time of enrollment.

Inclusion criteria for study cohortParticipant is 18 years or older at the time of enrollment.Participant is on mechanical ventilation at ICU admission, or is (expected to be) within 24 h thereafter, based on investigator’s judgment.Expected stay in ICU is 48 h or longer based on investigator’s judgment.
*S. aureus* colonization status is known within 72 h after start of first episode of mechanical ventilation and according to the result, the patient qualifies for enrollment.Written informed consent from subject / legally accepted representative within 72 h after start of first episode of mechanical ventilation.

Exclusion criteria for study cohortPrevious participation as a subject in the study cohort of this study.Simultaneous participation of the subject in any preventive experimental study into anti-staphylococcus or anti-pseudomonas aeruginosa interventions.Expected death (moribund status) within 48 h, or ICU discharge of the participant within 24 h, at the moment of informed consent.

### Study outcome definitions

Considering that the definition of our primary outcome, ICU pneumonia caused by *S. aureus* or *P. aeruginosa,* is very extensive, we would like to refer to the (Additional file 1: S.03) containing the full definition. In summary, ICU pneumonia is defined as pneumonia occurring ≥48 h after admission to the ICU and is confirmed by a new or worsening infiltrate on chest X-ray or CT-thorax. Furthermore, the patient must fulfill specific clinical criteria (for example abnormal temperature, production of sputum, auscultatory abnormalities, acute changes in the ventilatory support system), in addition to at least 1 microbiological criterion (positive respiratory specimen, blood culture, pleural fluid aspirate or lung tissue culture).

### Site selection

In total, 30 sites in 11 countries were selected from sources including but not limited to the COMBACTE CLIN-Net and LAB-Net databases [7]. To ensure the pan-European continent is represented, there is at least one country included from the Northern / Southern / Eastern and Western region of Europe. The selected sites adequately balance different factors such as geography, background antibiotic resistance prevalence, etc.. To ensure enrollment is met within the expected timelines, back-up sites were selected for various reasons (i.e. low enrollment numbers, decline further participation) that can supplement or replace primary sites selected. For each site also a local laboratory was selected to participate in the study.

A Site Selection Committee selected sites and laboratories based on pre-defined criteria in the Site Selection Plan. Assessment of these criteria was aided by site feasibility questionnaires. Participating ICUs must have a routine *S. aureus* screening protocol in order to be selected for participation.

Screening should consist of a minimum of one nasal swab and one lower respiratory tract (LRT) sample analyzed locally on the day of ICU admission. The LRT sample is defined as the collection of an endotracheal aspirate (ETA) sample, or, if an ETA cannot be collected, a sputum sample may be taken. As an exception, for routine *S. aureus* colonization screening at ICU admission only, if both the ETA and sputum cannot be collected, a throat swab may be taken.

### Statistical analysis

#### Sample size calculation

Sample size calculations are based on the expected incidence precision of *S. aureus* ICU pneumonia and *P. aeruginosa* ICU pneumonia, since the primary objective of the study is to identify the patient groups most at risk for this outcome.

Assuming an incidence of *S. aureus* ICU pneumonia of 12.5% and 1.5% in the *S. aureus* colonized group and non *S. aureus* colonized group respectively, this would result in an overall incidence of 7% within the 2000 study cohort subjects, or 140 *S. aureus* ICU pneumonia endpoints [9]. The overall incidence estimate would have precision of 1.12% (95% confidence interval [CI]: 5.9%–8.12%, using normal approximation).

For *P. aeruginosa* ICU pneumonia, the overall incidence is estimated regardless of colonization status at ICU admission. Assuming an overall incidence of *P. aeruginosa* ICU pneumonia of 2.5% within the 2000 study cohort subjects, this would result in 50 *P. aeruginosa* ICU pneumonia endpoints. The overall incidence estimate would have precision of 0.68% (95% CI 1.82%–3.18%, using normal approximation).

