### Enrichment strategy

In this study, 50% of the study cohort population is *S. aureus* colonized at ICU admission to ‘enrich’ the study population with *S. aureus* carriers (in nose or lower respiratory tract), while this naturally occurs in approximately 20–25% of the ICU population [10]. This was chosen as *S. aureus* carriage is being studied as one of the main known risk factors for subsequent *S. aureus* disease, thus without enrichment, the population needed for equal precision would be much larger [9, 11, 12]. However, the limitation of this choice is that one can argue that a population as such is not representative of the general ICU population, thus incidence estimation as well as assessing risk factors for *P. aeruginosa* ICU pneumonia may be suboptimal. We acknowledge this, and for this reason the surveillance population was included. Their data will allow distribution of baseline factors with the study cohort in an effort to assess the ubiquity of results across both groups. Furthermore, it can serve to identify potential bias between participants and non-participants. Considering that *P. aeruginosa* colonization at ICU admission is relatively rare and that colonization often occurs after ICU admission, no recruitment selection for *P. aeruginosa* colonized subjects will take place [13].

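### The planned overall *S. aureus* pneumonia incidence (7% ± 1.12 points) holds for the enriched 50:50 cohort only; the article states no step that converts it to incidence in the source ICU population

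*Protocol article*

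**What the plan says.** The Objectives section makes the incidence of *S. aureus* ICU pneumonia a primary objective and does not limit it to an enriched cohort.

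The Study cohort population section fixes enrolment at 1:1 by carriage at ICU admission, "with 1000 subjects in each stratum". The balance is kept over time by "selecting the first non-colonized subject after including a colonized subject".

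The Sample size calculation section bases the study size on the precision of incidence. For *S. aureus* it assumes 12.5% in carriers and 1.5% in non-carriers and states that "this would result in an overall incidence of 7% within the 2000 study cohort subjects". This gives 140 endpoints and a half-width of 1.12 points (95% CI 5.9% to 8.12%). It gives no precision for either stratum or for a natural mix of carriers and non-carriers.

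The Enrichment strategy section says of carriage, "while this naturally occurs in approximately 20–25% of the ICU population". It accepts that the cohort may not represent ICU patients in general and that incidence estimation may suffer. It gives this as the reason for including the surveillance population, whose data are to be used to compare baseline factors and to look for differences between participants and non-participants.

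The Planned analysis section names incidence density as the primary measure, with competing-risks and Cox-type models. It mentions stratification only as one way to handle clustering by readmission, ICU and country. Weighting by carriage is not mentioned.

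On use of the results, the Background says: "These objectives will directly contribute to the sample size and feasibility calculations for clinical trial design of the mAb interventions".

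**The concern.** An overall rate in a cohort stratified 1:1 is the average of two stratum rates in a ratio chosen by the design. Carriers are over-represented at least twofold (50% against 20–25%), and the plan assumes that they have about eight times the risk (12.5/1.5 = 8.3). The unweighted rate is therefore well above that of the population from which patients are drawn, and an interval placed around it is an interval for the wrong quantity if it is read as ICU incidence.

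This goes beyond silence on a detail. The article states the quantity on which the study is sized and also states a remedy for unrepresentativeness, and that remedy does not act on the estimate. Comparing baseline factors between cohort and surveillance patients would show the carriage imbalance created by the design but leave the incidence unchanged.

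At stake is a primary estimate that is meant to inform the sizing of later antibody trials. The same artificial mix also enters the association and prediction models unless carriage is kept in them. The Planned analysis section selects factors by Akaike's criterion and does not say that the sampling stratum is always retained.

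**Working it through.** **Inputs, all from the Protocol article**
- Stratum rates: carriers 12.5%, non-carriers 1.5% (Sample size calculation).
- Stratum sizes: 1000 and 1000 (Study cohort population).
- Natural carriage *w*: 20–25% (Enrichment strategy).
- Method: normal approximation, two-sided 95%, z = 1.96.

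**1. Reproduce the plan's figure**
- Overall rate: 0.5 × 12.5% + 0.5 × 1.5% = 7.0%.
- Events: 2000 × 0.07 = 140.
- Half-width: 1.96 × √(0.07 × 0.93 / 2000) = 1.118 points, giving 5.88% to 8.12%.

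The stated 7%, 140 endpoints and 1.12 points all reproduce.

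**2. Same stratum rates at natural carriage:** *w* × 12.5% + (1 − *w*) × 1.5%
- *w* = 20%: 2.50% + 1.20% = 3.70%. Ratio 7/3.70 = 1.89, so 7% is 89% higher (3.3 points).
- *w* = 25%: 3.125% + 1.125% = 4.25%. Ratio 7/4.25 = 1.65, so 7% is 65% higher (2.75 points).

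Both values lie below the lower limit of the planned interval (5.9%).

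**3. Precision by stratum**
- Carriers: 1.96 × √(0.125 × 0.875 / 1000) = 2.05 points.
- Non-carriers: 1.96 × √(0.015 × 0.985 / 1000) = 0.75 points.

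**4. Precision of the standardised overall rate from the same 2000 subjects:** 1.96 × √[*w*² × 0.125 × 0.875 / 1000 + (1 − *w*)² × 0.015 × 0.985 / 1000]
- *w* = 20%: 0.73 points (2.97% to 4.43%).
- *w* = 25%: 0.76 points (3.49% to 5.01%).

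These treat the carriage share as known and ignore clustering.

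**5. Does enrichment still pay?** The number of unselected patients needed for half-width *h* is 1.96² × p(1 − p) / *h*².
- To match step 4 at p = 3.70%, *h* = 0.729 points: about 2,580.
- To match step 4 at p = 4.25%, *h* = 0.763 points: about 2,690.

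Both exceed 2000, so enrichment improves the precision of the standardised overall rate.

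**The case against.** The case on the other side has real force.

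- **The 7% is labelled.** The article ties it to the study cohort and uses it to derive endpoints and precision. A reader might infer that the plan presents 7% as ICU incidence and so misstates it by 65–89%. The text does not say this. The gap arises only if the unweighted cohort rate is read as a population rate, although the unqualified wording of the primary objective makes that reading easy.
- **Weighting is unstated, not excluded.** This is a condensed article, and the full protocol and analysis plan are not shown. Standardisation may be specified there. What stands is narrower: the precision quoted is for the enriched mix, and the remedy described would not correct the overall rate.
- **The limitation is acknowledged.** The admission about representativeness is general. Whether the remark on incidence estimation covers *S. aureus* or mainly *P. aeruginosa* is unclear from the sentence. The surveillance population is named as the source population, so the design provides the basis for a correction.
- **Stratum results are partly in view.** Carriage is a named risk factor, and cumulative incidences are to be displayed by risk factors of interest.
- **The enrichment rationale stands.** A reader might infer that enrichment wins nothing, because ± 1.12 points would need only about 1,091 (p = 3.70%) to 1,246 (p = 4.25%) unselected patients. That comparison holds an absolute width fixed while the rate nearly halves. Step 5 of the working shows that the standardised estimate would need more unselected patients than the 2000 planned.
- **The downstream harm is conditional.** A trial in unselected patients planned on 7% would expect 39% to 47% too few events (1 − 4.25/7 and 1 − 3.70/7). No section says that the overall rate will be used that way; the article speaks of finding the patients at highest risk.

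**Conclusion.** The concern holds in a limited form. The planned 7% (5.9% to 8.12%) is correct arithmetic for a cohort fixed at half carriers. It does not estimate *S. aureus* pneumonia incidence in the source ICU population, which on the plan's own rates would be about 3.7% to 4.25%. The acknowledged limitation is paired with a remedy that would leave the overall estimate unchanged, and the article states no weighting.

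The size rests on three assumptions:
- The 20–25% carriage applies to the ventilated surveillance population with an expected stay of at least 48 hours.
- The 12.5% and 1.5% rates hold in that population.
- The comparison is on cumulative incidence. The primary measure is incidence density, where the ratio may differ if carriers and non-carriers contribute different time at risk.

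The choice to enrich is not at fault, and 2000 subjects are enough for the corrected estimate.

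**What to change.** 1. Make the carriage-specific incidences the main *S. aureus* results, with planning precision of 12.5% ± 2.05 points in carriers and 1.5% ± 0.75 points in non-carriers.
2. Report an overall incidence, or incidence density, only after standardising to the carriage share among eligible surveillance patients. For incidence density, weight both events and time at risk. The interval should reflect the stratified sampling, the clustering and, where it is estimated, the carriage share.
3. Restate the overall planning precision as about 3.7–4.25% ± 0.73–0.76 points, noting that the carriage share is treated as known and that clustering is not yet allowed for. If the 7% ± 1.12 points is kept, describe it as a property of the enriched cohort.
4. Keep the sampling stratum in the association and prediction models whatever the selection criterion suggests.
5. If the full protocol or analysis plan already specifies standardisation, say so in the Planned analysis and Enrichment strategy sections.

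The cost is a lower headline rate, a small weighting step and some rewording. No further patients are needed. One point must be confirmed first: participating ICUs must screen routinely for *S. aureus*, but the article says only that basic data are captured in surveillance. The sponsor should check that the screening result is recorded for every eligible surveillance patient.

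### Primary P. aeruginosa incidence is taken crude from a cohort fixed at 50% S. aureus carriers, and no stated step standardises it to the 20–25% carriage of the source ICU population

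*Protocol article*

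**What the plan says.** All references are to the protocol article.

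- **Objectives.** P. aeruginosa ICU pneumonia incidence through ICU stay is one of the two primary incidence objectives. The Background says the results will feed sample size and feasibility work for the antibody trials.
- **Study cohort population.** Carriers and non-carriers are enrolled 1:1, "with 1000 subjects in each stratum". Balance over time "will be managed by selecting the first non-colonized subject after including a colonized subject".
- **Sample size calculation.** For P. aeruginosa, "the overall incidence is estimated regardless of colonization status at ICU admission". The calculation runs: "Assuming an overall incidence of *P. aeruginosa* ICU pneumonia of 2.5% within the 2000 study cohort subjects", hence 50 endpoints and "precision of 0.68% (95% CI 1.82%–3.18%, using normal approximation".
- **Planned analysis.** Clustering by readmission, ICU and country is handled by frailty, stratification or robust variance. No weighting to the surveillance population is mentioned.
- **Enrichment strategy (Discussion).** Natural carriage is put at roughly 20–25%. The article accepts that the enriched cohort may not represent general ICU patients and that P. aeruginosa incidence may suffer. It says the surveillance population was included for that reason, and describes its use thus: "Their data will allow distribution of baseline factors with the study cohort in an effort to assess the ubiquity of results across both groups". It adds that these data can reveal bias between participants and non-participants.

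**The concern.** The cohort is a stratified sample with unequal sampling fractions: carriers make up 50% of it, against 20–25% of the patients it is drawn from. A crude proportion from such a sample estimates the source incidence only if the outcome is unrelated to the stratifying variable. For P. aeruginosa the article sets that variable aside and describes no step that restores the source mix.

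The estimate is meant to inform the design of later prevention trials, so what matters there is the incidence in the ICU population from which such trials would recruit. Comparing baseline factors between cohort and surveillance patients can show that the two differ. It does not turn the cohort figure into a figure for the source population. Frailty terms or robust variance deal with dependence within ICUs and likewise leave the carriage mix at 50:50.

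**Working it through.** **Inputs from the article.** N = 2000, with 1000 per carriage stratum; assumed P. aeruginosa incidence 2.5%; natural carriage c = 0.20 to 0.25.

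**Assumption (no figure in the article).** Ratio RR of P. aeruginosa risk in S. aureus carriers to that in non-carriers, taken over 0.5 to 2.

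**1. The article's own figure.** 1.96 × √(0.025 × 0.975 / 2000) = 0.684 points, giving 1.82% to 3.18% with 2000 × 0.025 = 50 events. This reproduces ±0.68. It is the formula for an unweighted simple random sample.

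**2. Error of the crude figure as an estimate for the source population.** With non-carrier risk p₀ and carrier risk RR × p₀, the cohort gives p₀(0.5·RR + 0.5) and the source has p₀(c·RR + 1 − c). Relative error = (0.5·RR + 0.5)/(c·RR + 1 − c) − 1.

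| RR | c = 0.20 | c = 0.25 |
|---|---|---|
| 0.5 | 0.75/0.90 − 1 = −17% | 0.75/0.875 − 1 = −14% |
| 0.8 | 0.90/0.96 − 1 = −6% | 0.90/0.95 − 1 = −5% |
| 1 | 0 | 0 |
| 1.25 | 1.125/1.05 − 1 = +7% | 1.125/1.0625 − 1 = +6% |
| 2 | 1.5/1.2 − 1 = +25% | 1.5/1.25 − 1 = +20% |

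In absolute terms, a crude 2.5% would correspond to a source incidence of 3.0% (RR 0.5) or 2.0% (RR 2) at 20% carriage, and 2.92% or 2.08% at 25%. For scale, the stated half-width is 0.684/2.5 = 27% of the estimate.

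**3. Precision of the carriage-weighted estimate.** Variance = c²p₁(1−p₁)/1000 + (1−c)²p₀(1−p₀)/1000. With p₁ = p₀ = 2.5% the ratio to the crude variance is 2[c² + (1−c)²].

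- c = 0.20: 2(0.04 + 0.64) = 1.36; effective N = 2000/1.36 = 1471; half-width 0.684 × √1.36 = 0.80.
- c = 0.25: 2(0.0625 + 0.5625) = 1.25; effective N = 1600; half-width 0.684 × √1.25 = 0.76.

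√1.25 = 1.12 and √1.36 = 1.17, so the interval is 12–17% wider. If stratum risks differ and the crude value stays at 2.5%, the same formula at c = 0.20 gives ±0.90 (RR 0.5) and ±0.67 (RR 2).

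**4. Does weighting pay?** At c = 0.20 the crude standard error is 0.35 points. The error at RR 0.5 or 2 is 0.5 points, so crude root mean squared error is √(0.35² + 0.5²) = 0.61. The weighted estimate, unbiased here, has standard error 0.90/1.96 = 0.46 (RR 0.5) or 0.67/1.96 = 0.34 (RR 2). At RR 0.8 the crude error is 0.17 points: total error is √(0.35² + 0.17²) = 0.39 crude against 0.43 weighted. At RR 1.25 both are 0.39. Weighting pays clearly when the association is strong and costs a little when it is weak.

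**5. Weighting by ICU as well.** Assume 30 equally busy ICUs, pairing within each ICU, no carriage effect inside an ICU, and incidence falling linearly from 4% to 1% as carriage rises (source value 2.5%).

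- Carriage 15–30%: crude 2.32%, total error √(0.18² + 0.34²) = 0.38; weighted by ICU and carriage 0.43 (half-width ±0.84).
- Carriage 10–35%: crude 2.20%, total error √(0.30² + 0.33²) = 0.44; weighted 0.47 (half-width ±0.93).

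In both, the bias removed is less than the variance added. A sharper split would reverse this. With two equal blocks of ICUs at 10% and 35% carriage and 4% and 1% incidence, the cohort shares are 0.222 and 0.778 and the crude figure is 0.222 × 4 + 0.778 × 1 = 1.67%.

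**The case against.** **Disclosure, and the plan that is not shown.** The article says openly that the cohort is not representative, ties the surveillance population to that problem, and may leave weighting to an analysis plan. This has force: nothing is concealed, and an unseen plan may add weights. What remains is that the article does fix a choice, estimation without regard to carriage, and that the uses it names for the surveillance data do not alter the estimate.

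**The precision figure is right.** It is. The sentence ties the 2.5% to the 2000 cohort subjects, and ±0.68 follows from that. A reader might infer an arithmetical error; there is none. The figure simply does not carry over to a standardised estimate.

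**The bias may be nil.** Also true. The article gives no P. aeruginosa risk by S. aureus carriage, and the range 0.5 to 2 is an assumption. For a ratio near 1 the crude figure is sound and has the smaller variance. That is a reason to show both figures, not to withhold the standardised one.

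**A stronger reading that the text does not support.** A reader might infer from "selecting the first non-colonized subject after including a colonized subject" that each ICU's share of the cohort follows its number of carriers, so that the estimate is also distorted across ICUs. Within-ICU pairing is the natural reading, but the article does not state it. Nor does it say that sites enrol without a cap. The distortion also needs P. aeruginosa incidence to move with carriage across ICUs. Choosing sites that differ in geography and resistance background implies variation in each, not correlation between them. A reader might likewise take the provision that "back-up sites were selected for various reasons (i.e. low enrollment numbers, decline further participation) that can supplement or replace primary sites selected" as adding to this distortion. It serves enrolment timelines, and the article gives no ground for tying it to carriage or for changing it.

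**Conclusion.** The point holds in a limited, conditional form. The article sets a primary incidence as a crude figure from a cohort with 50% carriers against 20–25% in the source, and states no correction. As an estimate for source ICU patients, the error is −17% to +25% for an assumed risk ratio of 0.5 to 2, about −6% to +7% for 0.8 to 1.25, and zero at 1. The documents do not show that the estimate is biased, only that it is unprotected against a bias the design makes possible and the surveillance population could largely remove.

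The ±0.68 stands for the enriched cohort. For a carriage-standardised estimate about ±0.76 to ±0.80 applies, for 25% to 20% carriage with equal risk in both strata. Distortion across ICUs is a possibility rather than a finding, and correcting for it trades bias against variance.

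**What to change.** 1. State that P. aeruginosa incidence, both density and cumulative, will be standardised to the carriage distribution of the surveillance population by weighting the two carriage strata, and reported next to the crude cohort figure.
2. Label ±0.68 as applying to the enriched cohort only. Give about ±0.76 (25% carriage) to ±0.80 (20% carriage) for the standardised estimate, with the equal-risk assumption stated.
3. Treat weighting by ICU as well as carriage as at most a sensitivity analysis.

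**Cost.** The change needs plan wording and modest programming, with no extra patients. The interval widens by about 12–17%. It also needs the carriage share among surveillance patients. Participating ICUs must screen routinely for S. aureus, so this should be obtainable, but the article does not say that screening results are recorded for every surveillance patient, and patients may refuse use of their data. Confirm availability first. If the share is known only approximately, show the standardised figure over 20–25%.
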